#### Data for Future Calculations

This study will provide data and information for future power calculations for larger cohort studies, including informative data types established by analysis of correlates with symptoms or outcomes of interest. An informative minimal data set can then be derived from this superset. This will also provide the unit cost of data collection for the full and minimal data sets for the planning of any future studies.

Remote monitoring provides the opportunity to continuously monitor patients in their daily lives outside of the hospital, with the potential to automate the detection of disease exacerbations and monitor the long-term evolution of disease trajectory. The acceptability and feasibility of remote monitoring using measures of heart and lung functions in patients with lung diseases are necessary first steps in this process, which this study aims to evaluate.

## Methods

### Study Design: Methods of Data Collection

#### RADAR-Base mHealth Platform

##### Active Data Collection

The Active Remote Monitoring Technology (aRMT) app (Android and iOS) will be used to collect data from patients by issuing questionnaires and tests that require some conscious action to perform. These will include questionnaires for participant QoL and mental health (GAD-7 and PHQ-8) and disorder-specific questionnaires for symptom tracking of COPD (COPD Assessment Test), ILD (Living with Idiopathic Pulmonary Fibrosis assessment), and posthospitalization COVID (PCFS, CCLTE list, and WHO COVID-19 symptoms list). These are summarized in Table 2. Participants will be issued a notification (at the appropriate time) that will open the corresponding questionnaire to be filled on the mobile app. Further to the scheduled questionnaires, the app will be used to generate dynamic notifications for questionnaires to validate the performance of symptom classification and prediction in near real time. Details of the aRMT mobile app are provided in Figure 2.

This study will also include a battery of experimental digital tests to explore the potential to assess lung breathing function through the use of audio capture or other interactive means. Audio data are readily available through the phone’s built-in microphone (or the addition of an auxiliary Bluetooth microphone for improved or standardized sound capture). Participants will be issued a notification to complete the relevant task, and selecting this will open the corresponding test on the mobile phone with instructions on how the test is to be performed. Active audio tasks, such as pronouncing sustained vowels and counting from 1 to 20, will provide additional information on voice production dynamics that might be affected by lung disorder symptoms. A lung sound test, which will record audio during breathing by placing the microphone against the chest during a sequence of breaths [42,43], might be evaluated in a further study based on this protocol.

Furthermore, the audio tasks will be validated in conjunction with patient tests and protocol development to ensure that they capture relevant information. Quality assurance mechanisms will be implemented to ensure that incoming audio signals are valid (eg, checking if the signal-to-noise ratio is within an acceptable scope or if the voice is contained within a sample).

**Table 2 table2:** Remote monitoring measures.

Remote monitoring parameter		Data source	Collection frequency	Cohort	Purpose
**Speech and audio**					
	Speech – Active Remote Monitoring Technology (aRMT)	Digital test/aRMT phone app	Weekly	All	Voice production tasks via the phone. These tasks will assess change in the phonatory-respiratory system [3].
**Activity, functioning, and fatigue**					
	Activity	Wrist wearable device	Continuous	All	Measure exercise levels, and combine and compare heart rate (HR) for the measurement of proportional nonresting HR. Impacts on lifestyle, including physical activity and mobility [27].
	Sleep parameters	Wrist wearable device	Continuous	All	Evaluation of the duration and quality of sleep [28].
	Fatigue severity scale	Questionnaire/aRMT phone app	Weekly	All	Subjective experience of fatigue [29].
	Passive fatigue measure	Wrist wearable device	Continuous	All	Heart rate variability (HRV), time to bed, and Garmin Body Battery level [30,31].
**Cardiopulmonary**					
	HR	Wrist wearable device	Continuous	All	Continuous measure of baseline HR for (1) resting HR (sedentary and sleeping), (2) nonresting HR (under light, medium, and high activity or stair climbs), and (3) cardiopulmonary performance [32].
	HRV	Wrist wearable device	Continuous	All	Continuous measure of the variation in time intervals between consecutive heartbeats. Low resting HRV is an indication of high levels of physical or mental stress [33].
	Respiratory rate	Wrist wearable device	Continuous	All	Respiration rate [34].
	Pulse oximeter (SpO_2_)	Wrist wearable device (continuous)	Continuous (nighttime)	All	Blood oxygenation as measured by PhotoPlethysmoGram sensors on the wrist wearable device; this measurement should be continuous at least during the nighttime [35].
	Pulse oximeter (SpO_2_)	Finger pulse oximeter (periodic)	Daily	All	Periodic assessment with a clinically approved finger-worn device will be provided to validate the daily measure and may be included for dynamic spot checks.
	Breathing	Digital test/aRMT phone app	Weekly	All	Measure lung function and volume by inspiration and expiration using tests delivered through the aRMT app and audio capture.
	Spirometry	Spirometer	Daily	All	Lung function measurement.
**Questionnaires - Symptoms, mental health, quality of life (QoL) (aRMT)**					
	Post-COVID-19 functional status (PCFS) scale	Questionnaire/aRMT phone app	Weekly	COVID-19	Establish post COVID-19 functional status [36].
	CDC COVID-19 long-term effects (CCLTE) (aRMT)	Questionnaire/aRMT phone app	Daily	COVID-19	Establish the degree of long-term COVID-19 effects [15].
	WHO COVID-19 symptoms (WCS) list (aRMT)	Questionnaire/aRMT phone app	Daily	COVID-19	Establish the degree of persistent COVID-19 symptoms [37].
	COPD assessment test (CAT)	Questionnaire/aRMT phone app	Cohort: Daily	All	CAT to measure the impact of COPD on a person’s life. It is unidimensional, and assesses cough, sputum, dyspnea, and chest tightness. Eight questions [38,39].
	Idiopathic pulmonary fibrosis patient-reported outcome measure	Questionnaire/aRMT phone app	Weekly	Interstitial lung disease (ILD)	ILD QoL self-report.
	Living with idiopathic pulmonary fibrosis	Questionnaire/aRMT phone app	Daily	ILD	ILD QoL self-report.
	Visual analog scale (VAS) cough	Questionnaire/aRMT phone app	Monthly	ILD	Score symptoms (cough).
	St. George’s Respiratory Questionnaire (SGRQ)	Questionnaire/aRMT phone app	Quarterly	All	Assess the impact of overall health, daily life, and well-being in patients.
	Pittsburgh Sleep Quality Index (PSQI)	Questionnaire/aRMT phone app	Monthly	ILD	Sleep scoring questionnaire.
	Exacerbation rating scale (ERS)	Questionnaire/aRMT phone app	Dynamic/on demand	All	A confirmatory rating scale for detected exacerbations in real time; participants will be sent notifications to complete these.
	Generalized Anxiety Disorder scale (GAD-7) and Patient Health Questionnaire depression scale (PHQ-8) (aRMT)	Questionnaire/aRMT phone app	Fortnightly	All	Establish depressive and anxiety symptoms [40,41].
**Electronic case report form (eCRF) and surveys**					
	Epworth sleepiness scale	eCRF REDCap	Baseline	All	Used to diagnose obstructive sleep apnea (OSA).
	STOPBang questionnaire	eCRF REDCap	Baseline	All	Used to diagnose OSA.
	MRC breathlessness	eCRF REDCap	Baseline	All	Dyspnea scale that is used to evaluate the impact of breathlessness on daily activity.
	Demographics	eCRF REDCap	Baseline	All	Patient demographics form.
	Study information	eCRF REDCap	Baseline	All	Study-related information collected at baseline, for example, phone and device registration, and administrative information.
	Contact information	Local Site File	Baseline	All	Contact information.
	Technology Assessment Measurement Fast Form	eCRF REDCap	End of study	All	Measure the impact of the technology being used and evaluate its acceptability, usability, and performance.
	Experience of participation	eCRF REDCap	End of study	All	Exit interview (semistructured).

**Figure 2 figure2:**
[figure not shown]
The Active Remote Monitoring Technology (aRMT) app used to collect phone-delivered questionnaires. Top: app screens and example questionnaire. Bottom left: Example notification to complete the questionnaire. Bottom right: Speech task.

##### Passive/Background Data Collection

Garmin Vivoactive 4 is the selected wrist-worn wearable device. Several parameters of interest are reported continuously by the wearable device, including activity (steps and exercise as calories consumed), sleep, fatigue, HR, fatigue levels (Garmin Body Battery), HR variability, respiratory rate (RR), and pulse oximetry (SpO_2_) (Table 2).

Additional periodic data collection will be done with finger pulse oximetry and spirometry (Table 2). Participants will receive a notification to carry out pulse oximeter and spirometry tests at a convenient time on a daily basis, and values will be recorded on the aRMT app.

#### Data Sources

Data sources used in this study include wearable devices, mobile phone apps, and questionnaires. All the measures collected are shown in Table 2.

#### Clinical Data

Participants will be requested to consent to their medical records (routine clinical and GP records; via the clinical team) and anonymized data being made available to the study team throughout the study. Where possible, specific data sets from routinely acquired clinical records may be included.

### Data Analysis

Multimedia Appendix 1 summarizes the data analysis algorithms and models under consideration in this study.

Analyses are intended to assess the feasibility of the RADAR-Base platform for lung disorder remote monitoring (including the quality of data, the cross-section of passive and active data, data completeness, the usability of the system, and the acceptability of the system).

We will generate descriptive statistics for demographics, attrition rate, and the number of participants using the remote assessment measurements without loss or damage and providing adequate quantity and quality of data, and for the duration of the study period.

Using classification/regression/machine learning approaches, we will investigate whether any demographics and/or other numerical information obtained during the baseline and longitudinal data collection periods of the study might serve as predictors for subject dropout and the percentage of adequate data.

We will establish the appropriate setup of data collection and the parameters of the study, which would be required to conduct a future larger longitudinal study.

Feasibility and acceptability of the wearable device will be assessed by answering the following questions: (1) Are the sensors on the device (not a gold standard) feasible and acceptable to conduct remote monitoring of pulmonary diseases? (2) Is Garmin a feasible device for measuring changes in key physiological parameters such as HR and SpO_2_? These will be evaluated against the gold standard device (pulse oximeter and spirometry).

The feasibility of the symptom questionnaire will be evaluated against the gold standard from spirometry. Technology Assessment Measurement Fast Form (TAMFF) plus the experience of participation exit interviews will be used to determine the overall feasibility and acceptability of the technology and the protocol used in the study.

If adequate data are collected in the pilot, we aim to explore methods to establish the feasibility of the data collection apparatus as a means to study disease trajectory and patient stratification.

This will involve using data involving HR, SpO_2_, sleep, activity, respiratory rate, questionnaires, and other collected measures to model participant stratification and differential disease trajectory.

We will explore the identification of acute clinically interesting events, such as exacerbations and rapid changes in clinical conditions or physiological data streams.

We will use the pulse-respiration quotient [44] and pulse-activity quotient as measures of the changes in respiration efficacy and exacerbation.

We will adopt machine learning approaches to perform both cross-sectional and individualized classification for the identification of events, such as exacerbations, using a questionnaire or other active data as labels providing context to passive data streams such as HR, SpO_2_, respiratory rate, and others.

Using multimodal data sets, we will characterize the periods of time around acute events, such as exacerbations, to include the pre-exacerbation period, period during exacerbation, and postexacerbation period.

We will investigate the potential of the data collected to identify putative subclinical exacerbations or other lower level fluctuations in participant symptoms.

If adequate numbers of events are generated in the study, an opportunity to apply anomaly/novelty detection methods will be possible. In this way, we will use these approaches to learn the baseline state for the participants and establish significant deviations from this.

Using the real-time aspect of the data collection, we will use the real-time ERS to acquire real-time responses to evaluate and assess the performance of a model for exacerbation detection and refine an individual-level model for exacerbation detection.

Since we do not have enough prior data, we plan to consider real-time anomaly detection methods and preprocess the data based on prior knowledge. The models will be pretrained on a daily schedule (using previous N days of data; N is yet to be decided but is initially considered 21 days) and will be ready for running inferences in real time (using wearable sensor data as inputs collected in real time) and taking actions based on the results of the inferences (sending an ERS assessment through the aRMT app) to acquire responses at the time of the event to assess the performance of the model.

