### Outcomes

#### Acceptability of the Remote Monitoring System in the Three Disease Areas

The acceptability of the platform will be determined in terms of recruitment, retention, data completeness, and the qualitative experience of participants. The exit survey Technology Assessment Model Fast Form (TAM-FF) will also be used to evaluate the data collection infrastructure with participant feedback. The study will test both the feasibility and acceptability of tasks for participants. On completion of the data collection period, we will measure the total available data as a function of a theoretical maximum and assess data quality measured by a range of criteria, including missingness and contiguity.

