#### Sample Size

The study will include 20 participants for each of the three disease areas. This is a small sample feasibility study to assess the practical use of remote monitoring in three lung disease areas. The sample size will adequately allow objective assessment of the system deployed for this type of data collection in the typical patient population.

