##### COPD

We will recruit 20 patients with COPD from our services in London and follow them for up to 6 months or until the first exacerbation, whichever is sooner. We will recruit patients with a history of exacerbations to increase the likelihood of identifying patients who would experience events during the study. We will analyze whether monitoring is able to detect exacerbations earlier than the current gold standard (patient reporting to a clinician) and therefore could be used to help patients get treatment earlier.

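### Predictors of dropout and of adequate data may come from the same period in which those outcomes accrue, so features that count data can show prediction where there is none

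*Protocol article*

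**What the plan says.** In the Protocol article, the Data Analysis section plans to explore whether demographics or numeric data of any kind "obtained during the baseline and longitudinal data collection periods of the study might serve as predictors for subject dropout". The same sentence names a second outcome, the share of data that is adequate. The method is left open across regression, classification and machine learning. No cut-off date for predictors is given, and no type of numerical feature is set aside.

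The Outcomes section on acceptability says when and how completeness is measured: once data collection is over, "we will measure the total available data as a function of a theoretical maximum". It also makes retention part of acceptability.

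Two design facts matter here. Under Sample Size, "The study will include 20 participants for each of the three disease areas", so 60 in all. Under Participant Cohorts, ILD/IPF participants are followed for 6 months, while COPD participants are followed "up to 6 months or until the first exacerbation, whichever is sooner". Observed time in the COPD cohort therefore varies by design as well as by dropout.

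**The concern.** A participant who leaves stops producing data. Any feature that grows with time in the study, such as questionnaires completed, days with wearable data or a summed score, is lower in leavers simply because they left. If it is taken from the longitudinal period without a cut-off and then used to predict leaving, the direction of inference is reversed. For the percentage of adequate data the overlap is closer still, because the amount of data collected is what that percentage measures.

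The Primary Objective names dropout rates as a basis of evaluation, and the Data Analysis section goes on to say that the study will set the parameters of a larger one. A feature reported as predicting dropout could be carried into that planning although it says only that people who left gave less data.

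**Working it through.** The plan gives no AUC, power or expected dropout rate for this analysis, so there is no figure to reproduce. The check asks what each kind of feature would show if dropout had no predictor at all.

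**Inputs from the document:** 60 participants (3 × 20) and 6 months of follow-up, taken as 180 days.

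**Assumptions:**
- All three cohorts run the full 180 days.
- Dropout by 6 months is 10%, 20% or 40%, that is 6, 12 or 24 of 60.
- Time to dropout is exponential and independent of every participant trait.
- Each person's daily chance of giving data is drawn from Beta(8,2), with mean 8/(8+2) = 0.8.
- A daily score has between-person SD 5 and within-person SD 3.
- Adequate data is read as days with data divided by 180, in line with the completeness outcome. The article does not define the percentage separately.

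**The mechanism by hand.** A completer gives on average 0.8 × 180 = 144 days of data. A participant of the same adherence who leaves at day 90 gives 0.8 × 90 = 72. The count separates the two although nothing about them differs beforehand.

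**Simulation.** 1000 cohorts per dropout rate. AUC is for a lower value indicating dropout; 0.50 is the correct answer throughout.

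| Feature over all observed follow-up | AUC, 10% dropout | 20% | 40% |
|---|---|---|---|
| Count of days with data | 0.923 | 0.926 | 0.936 |
| Cumulative score | 0.864 | 0.871 | 0.884 |
| Maximum score | 0.563 | 0.570 | 0.568 |
| Within-person SD | 0.514 | 0.513 | 0.520 |
| Per-day mean | 0.504 | 0.507 | 0.500 |
| Last value | 0.502 | 0.504 | 0.500 |
| Baseline value | 0.501 | 0.507 | 0.500 |

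**Correlation with adequate data (Spearman).** The day count gives 1.00, because dividing by 180 leaves the ranking unchanged. The cumulative score gives 0.59, 0.68 and 0.81. The per-day mean gives 0.00, 0.01 and 0.00.

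**With a landmark.** The features were then restricted to days 1 to 30, among those still enrolled at day 30, with outcomes counted afterwards. The AUC of the day count for dropout becomes 0.501, 0.502 and 0.504. The early count still correlates with the later amount of data (0.72, 0.62, 0.44). That is real prediction, because adherence was simulated as a stable personal trait.

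**COPD stops and the denominator.** A COPD participant with 0.8 adherence whose follow-up ends at an exacerbation on day 90 has 72 days of data. Over 180 days this is 72/180 = 40%; over the follow-up that was planned for that person it is 72/90 = 80%. The choice of theoretical maximum decides which is reported.

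**The case against.** The sentence lists sources of candidate variables and does not say that each is summarised over the whole of follow-up. A value measured before dropout, or a time-updated covariate, would fit the wording too. The article names no count feature as a predictor; its measures are mainly physiological values and questionnaire scores, whose averages are unaffected. The analysis is exploratory, no decision rule rests on it, and an analysis plan or the algorithms appendix, neither shown, may fix the time order.

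Most of this stands, and it limits the point. What it does not remove is that the stated window includes the outcome period and the stated candidate set is unrestricted. The article was not too condensed to give time order: for the exacerbation models the same section trains on preceding days, initially 21, and infers afterwards.

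Three stronger readings are tempting and are not supported:
- A reader might infer that the predictors contain the outcome and that apparent prediction is guaranteed. Baseline variables, per-day means and last values gave AUCs of about 0.50, so this is true only of some features.
- A reader might infer that 60 participants and an open predictor list mean overfitting will be reported as prediction. The article does not say that in-sample performance will be reported. Predictor lists, penalisation and cross-validation are commonly left to the analysis plan.
- A reader might infer that COPD stops at first exacerbation will be counted as dropout. The COPD section defines them as the planned end of follow-up, and nothing in the article calls them dropout.

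**Conclusion.** The point holds for features that measure data quantity. As written, the plan allows them as predictors of outcomes that they partly or wholly restate. With no true predictor, the simulated AUC for dropout is about 0.86 to 0.94 for count and cumulative features. The day count is the same quantity as the completeness outcome apart from a constant divisor. Maxima are slightly affected (0.56 to 0.57), and averages, last values and baseline items are not.

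These sizes rest on assumed dropout, adherence and follow-up, but the pattern is stable across dropout of 10% to 40%. Reading the predictor window as all of follow-up is natural but not the only possibility. The consequence for the follow-on study is inferred. The descriptive reports of attrition and completeness are not affected. This is a worthwhile and cheap correction to an exploratory analysis.

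**What to change.** State in the Data Analysis section that predictors of dropout and of adequate data must precede the outcome:

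- Use only baseline data and data from an early fixed window. Days 1 to 28 would match the 1-month support call described under Protocol Compliance; the exact day is a choice.
- Include participants still enrolled at the end of that window, and count dropout and the percentage of adequate data only from then on.
- End the denominator of that percentage at each participant's planned end of follow-up, so that a COPD stop at first exacerbation counts as completion.
- List dropouts before the landmark descriptively.

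Time-updated predictors measured before dropout are an acceptable alternative and keep early dropouts in the model.

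The change is to analysis wording only. Its cost is the early dropouts that are no longer modelled. Under the same constant-rate assumption their expected number by day 28 is 60 × [1 − (1 − d)^(28/180)]. This is about 1 of 6 dropouts at d = 10%, 2 of 12 at 20% and 5 of 24 at 40%. More would be lost if dropout is concentrated in the first weeks.
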